### Trial design {8}

The FOVOCIP study is a randomized, open-label, phase III clinical trial with a non-inferiority design, in which patients are randomized in a 1:1 ratio into two parallel, controlled prophylaxis groups: fosfomycin or ciprofloxacin. The groups are stratified by site and by underlying disease (acute leukemia or stem cell transplantation).

FOVOCIP is a pragmatic study and very well adapted to the usual clinical practice of the sites of the public health system in Spain.

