## Methods: participants, interventions, and outcomes

### Study setting {9}

The sponsor of this study is FINBA and plans to include 156 patients over 2 years; therefore, 11 Spanish national hospitals are needed to achieve the described objective.

The hospitals included are:✓ University Hospital Central of Asturias.✓ University Hospital La Paz.✓ University Clinic Hospital San Carlos.✓ Hospital San Pedro of Alcántara.✓ University Hospital Morales Messeguer.✓ University Hospital La Fe.✓ University Clinic Hospital of Valencia.✓ University Hospital of Málaga.✓ University Hospital Fundación Jiménez Díaz.✓ University Clinic Hospital Lozano Blesa.✓ University Hospital of Burgos.✓ These are academic hospital centers with experience in the management of acute leukemias and stem cell transplants. They are located around several regions in Spain. Therefore, they represent a broad spectrum of our country geography. This guarantees the representativeness of the Spanish population and the achievement of the planned recruitment.✓ The Clinical Trials agency and SCReN (Spanish Clinical Research Network) were responsible for obtaining authorization from the local ethics committee (EC) and notifying to the Spanish Agency of Medicines and Medical Devices of the start-up of the study.

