## Assignment of interventions: allocation

### Sequence generation {16a}

The randomization will be carried out by the electronic clinical registry (eCRF) called MACRO. The management of the electronic tool is carried out by the SCReN clinical research platform work-package.

After inclusion, the randomization list included in the eCRF will automatically assign the case to the control or experimental group in 1:1 ratio. Candidates are stratified according to their baseline disease: acute leukemia or HSCT.

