## Statistical methods

### Statistical methods for primary and secondary outcomes {20a}

This phase 3 trial will compare the efficacy of fosfomycin with that of ciprofloxacin in preventing the occurrence of at least one episode of neutropenic fever of infectious origin in a randomized non-inferiority design.

The primary endpoint is febrile neutropenia of infectious origin. This analysis will be performed in the intention-to-treat (ITT) and in the per-protocol population (PP). The ITT population is defined as all patients who are eligible and randomized. The PP population consists of all patients who do not have major protocol deviations, as determined by the study PI, and have received prophylactic drugs for at least of 24 h.

The rate of febrile neutropenia will be compared between the 2 arms with a chi-square test with 2-sided alpha of 0.05. The difference in the proportion and the associated 95% CIs will be provided. If, within either patient arm, the data suggest a possible difference in baseline incidence between the randomization strata, we will consider Cochran-Mantel–Haenszel test to examine the association between the incidence of febrile neutropenia and the study treatment with adjustment for the randomization strata. Logistic regression models will be performed to evaluate the treatment effect on the incidence of febrile neutropenia adjusting for stratification and other baseline patient characteristics.

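### The only interval that can be set against the 5-point margin ignores the disease stratum, and the document gives two accounts of what the strata are

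*Protocol article*

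**What the plan says.** **Stratification factors.** Trial design {8}: "The groups are stratified by site and by underlying disease (acute leukemia or stem cell transplantation"). Sequence generation {16a}, which describes how the eCRF list allocates patients, has: "Candidates are stratified according to their baseline disease: acute leukemia or HSCT". It does not mention site. Study setting {9} says that "11 Spanish national hospitals are needed to achieve the described objective".

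**Primary comparison.** Statistical methods {20a}: "The rate of febrile neutropenia will be compared between the 2 arms with a chi-square test with 2-sided alpha of 0.05". It adds: "The difference in the proportion and the associated 95% CIs will be provided". Both are unstratified and unconditional.

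**Stratified test.** The same section continues: "If, within either patient arm, the data suggest a possible difference in baseline incidence between the randomization strata, we will consider" a CMH test of the association between "the incidence of febrile neutropenia and the study treatment with adjustment for the randomization strata". It gives no threshold for the trigger and does not say whether CMH would replace the chi-square test or sit beside it.

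**Adjusted model.** Logistic regression adjusting for stratification and other baseline characteristics is planned in {20a} without any condition.

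**Margin.** Sample size {14} sets 5 percentage points, with expected success of 17% on ciprofloxacin and 30% on fosfomycin, and 67 evaluable patients per arm.

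**The concern.** Non-inferiority is judged by an interval for a difference in proportions against 5 points. Three features of the plan weaken that interval or its supporting analysis.

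1. When allocation is balanced within disease groups and disease affects the outcome, the crude variance formula counts between-stratum variation that the design has removed. The interval is then wider than it need be.
2. The stratified alternative is a test of association. It yields no stratified risk difference, so even if it is used the margin is still judged on the crude interval. The logistic model, as described, gives no risk difference either.
3. The trigger is the primary outcome tabulated by stratum within arm, with no cut-off, and the strata are defined differently in two sections. The adjusted analysis is therefore not fixed in advance. Treatment is open-label, so a fixed rule has value.

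**Working it through.** **1. Reproduce the stated sample size.** Inputs from {14}: 0.17, 0.30, margin 0.05, power 80%, alpha 0.05.

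Crude V = 0.17 × 0.83 + 0.30 × 0.70 = 0.1411 + 0.2100 = 0.3511. Distance to the margin = 0.13 + 0.05 = 0.18.

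n per arm = (1.645 + 0.842)² × 0.3511 / 0.18² = 67, as stated. This uses one-sided 0.05. With a 95% CI (one-sided 0.025) the same formula gives 86. That is a separate matter, and it enters here only because {20a} specifies a 95% CI, so power below is computed with 1.96.

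**2. Number of strata.** Disease only: 2 cells, 156 / 2 = 78 patients each if evenly split. Site by disease: 11 × 2 = 22 cells, 156 / 22 = 7.1 patients each, about 3.5 per arm.

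**3. Power of the crude 95% CI at 67 per arm.** SE = √(0.3511 / 67) = 0.0724. Power = Φ(0.18 / 0.0724 − 1.96) = Φ(0.53) = 0.70.

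**4. Power of the disease-stratified 95% CI.** The document gives no success rates by disease. Assumption: two equal strata 20 points apart, with the same 13-point treatment difference in each. Control is then 7% and 27%, fosfomycin 20% and 40%.

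- Control: (0.07 × 0.93 + 0.27 × 0.73) / 2 = (0.0651 + 0.1971) / 2 = 0.1311
- Fosfomycin: (0.20 × 0.80 + 0.40 × 0.60) / 2 = (0.16 + 0.24) / 2 = 0.2000
- V = 0.3311; ratio to crude = 0.3311 / 0.3511 = 0.943, about 6% smaller
- SE = √(0.3311 / 67) = 0.0703; power = Φ(0.18 / 0.0703 − 1.96) = Φ(0.60) = 0.73

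In patients: 67 × 0.3511 / 0.3311 = 71, so the crude analysis would need about 4 more per arm for the same precision. With no gap between strata, V stays at 0.3511 and nothing changes.

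**5. Does the data-driven choice inflate error?** Simulation: 200,000 runs per scenario, 33 and 34 patients per stratum in each arm. The trigger was assumed to be p < 0.10 between strata in either arm, because the document gives none. Error is for non-inferiority at the margin (nominal 0.025); power is at +13 points.

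| Control success by stratum | Error: crude / stratified / data-selected | Power: crude / stratified / data-selected |
|---|---|---|
| 17%, 17% | 0.030 / 0.030 / 0.030 | 0.70 / 0.71 / 0.70 |
| 10%, 24% | 0.027 / 0.030 / 0.030 | 0.70 / 0.72 / 0.72 |
| 8%, 30% | 0.024 / 0.030 / 0.030 | 0.68 / 0.71 / 0.71 |

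A 40/27 split of strata gives the same pattern, with error up to 0.031 for both the stratified and the data-selected interval. Two-sided type I error of the data-selected test is 0.049 to 0.050 throughout.

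**The case against.** **A reader might infer that choosing the test after seeing the data inflates the false-positive rate.** The simulation does not support this. With two strata, the data-selected analysis has the same error as always stratifying. The stratified interval is if anything slightly more liberal than the crude one when a gap exists (0.030 against 0.024 to 0.027), so part of the power gain is the removal of the crude interval's conservatism.

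**A reader might infer that nothing is adjusted unless the trigger fires, or that two primary results compete.** The text does not say so. The logistic regression is unconditional, the crude difference and CI are always reported, and nothing states that CMH would replace them. The estimate set against the margin is fixed; it is fixed without the stratum.

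**The gain is modest and assumed.** This stands. No rates by disease are given. A larger gap would show a larger gain, but 30 points implies 2% success in one control stratum, fewer than one expected success in about 33 patients. The normal approximation cannot carry that, so it is not used here.

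**The analysts are blinded ({17a}).** This limits steering, but does not supply a threshold or a role for the CMH test.

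**The article may simply have dropped site from {16a}, and Mantel-Haenszel methods tolerate sparse cells.** Both are possible. Small cells alone do not invalidate CMH, and {16a} does not say that disease is the sole factor. The hospital number in the patient code ({16c}) does not settle it, since that is an identifier. Two printed statements still name different factors, and {20a} depends on which is right.

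**Conclusion.** The point holds as one of efficiency, consistency and prespecification. The factors in {8} and {16a} differ, so the strata invoked in {20a} are 2 or 22 cells. The interval that decides non-inferiority omits disease, which is a randomisation factor under either account, and neither planned adjusted analysis supplies a risk difference to put in its place.

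The size is small to moderate: about 6% of variance and about 3 points of power (70% to 73%), assuming equal disease strata 20 points apart, a constant 13-point effect and 67 per arm. The simulated gains at gaps of 14 and 22 points are about 2 to 3 points. If disease is not prognostic, the loss is zero. The documents do not support a claim of lost error control.

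**What to change.** - Name one primary analysis: the Mantel-Haenszel risk difference stratified by underlying disease, with its 95% CI compared with the 5-point margin. This works whichever account of the randomisation is right.
- Delete the condition that makes stratification depend on the observed outcome by stratum. Keep the crude difference and CI as supportive, and the logistic model as secondary.
- Check {8} and {16a} against the list programmed in the eCRF and state the same factors in both. If site was a factor, handle it in a sensitivity analysis and not through 22 cells in the primary one.

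The cost is wording in the protocol, and in the SAP if it repeats the rule. No new data or patients are needed, because disease is already recorded for randomisation. Trial status reports 106 patients recruited, and an interim look is planned before that number. The change should therefore be dated and should record that those making it had not seen outcomes by arm.

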#### Outcomes {12}

The primary endpoint is febrile neutropenia requiring antibacterial treatment.Fever is defined as a single oral temperature of 38.3 °C or a temperature of 38 °C sustained over a 1-h period.

If the patient is receiving any medication highly likely to induce fever or has previously received a transfusion, at least one positive culture or infectious focus will be required for fever to be attributed to infection.

When febrile neutropenia occurs and infection is suspected, prophylactic antibiotics will be discontinued and evaluation and therapy will be administered according to standard and local guidelines.

Secondary endpoints are as follows:Documented infections. They will be classified according to Han’s criteria in one of these categories: microbiologically documented infection (bacterial viral or fungal), mixed infection, clinically documented infection, and possible infection (fever of unknown origin).The amount of concomitant antibiotics prescribed in addition to prophylactic drugs will be measured as a ratio of antibiotic days per days of hospitalization. Antibiotics will be classified according to the watch/reserve classification (21).Overall survival will be defined as the time from the day of randomization to the date of death (whatever the cause of death) or to the completion of the study. Fever-free survival will also be determined.

Safety will be assessed by the incidence, severity and type of adverse events (AEs), and by the microbiological assessments:

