### Sample size {14}

The reviewed clinical trials and meta-analyses have consistently shown that 65% of patients receiving prophylactic the fluoroquinolones levofloxacin and ciprofloxacin will develop infectious fever (2,17,18) which is consistent with success rate of 35%. Considering that the actual rate of resistance to fluoroquinolones is established to be around 50%, we anticipate a success rate of 17% and 30% in the active control and active and experimental control arms, respectively.

If a non-inferiority margin of 5% is defined, one hundred and thirty-four patients (67 in each arm) will be needed to demonstrate non-inferiority of fosfomycin versus ciprofloxacin with 80% potency and an alpha level of 0.05.

Considering that 15% of the enrolled patients will be ineligible or unable to be evaluated, the maximum number of study participants will be 156: 78 patients in each arm.

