The analysis of the secondary endpoints will be performed as follows:Rate and type of documented infections with 2-sided alpha of 0.05. Again, logistic regression models will be performed to evaluate the treatment effect on the incidence of each event adjusting for stratification and other baseline patient’s characteristics.Amount of concomitant antibiotic utilization. The analysis will be performed with a 2-sample *t*-test or the Mann–Whitney *U* test if the distribution is non-normal.Survival will be analyzed using the Kaplan–Meier estimate. The K-M survival curves and medians (if estimable) along with their 2-sided 95% CIs will be provided for each treatment arm. The log-rank test will be used to compare treatment arms. Differences in survival without fever will also be assessed with a log-rank test at the 5% significance level.Adverse events. This end point is included in the safety analysis and will be performed in the SP. AE will be categorized as severe and non-severe, as this classification determines the notification procedure. Intensity of AE will be evaluated according to the National Common Terminology Criteria for Adverse Events (NCI CTCAE), version 5.034.

The microbiological safety assessments will be analyzed as specified in item 33.

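### The adjusted logistic model prescribed for each infection category is unreliable where a category is rare (about 5% of patients or fewer), and fixed site terms would add bias

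*Protocol article*

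**What the plan says.** Documented infections are the first secondary endpoint. Outcomes {12} classifies them as "microbiologically documented infection (bacterial viral or fungal), mixed infection, clinically documented infection, and possible infection (fever of unknown origin"). Counting bacterial, viral and fungal separately, that is about six categories.

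Statistical methods {20a} plans the comparison as "Rate and type of documented infections with 2-sided alpha of 0.05" and adds that "logistic regression models will be performed to evaluate the treatment effect on the incidence of each event adjusting for stratification" and for other baseline characteristics. The covariates are not named.

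Two further statements set the size of the problem. Sample size {14} states that "the maximum number of study participants will be 156: 78 patients in each arm". Trial design {8} says "The groups are stratified by site and by underlying disease", and Study setting {9} lists 11 hospitals. Sequence generation {16a}, however, names only baseline disease as a stratification factor, so the article does not settle whether adjusting for stratification means one term or eleven.

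**The concern.** The article assigns the same adjusted model to every category, whatever its frequency. A category with a handful of events cannot support an ordinary logistic model with arm, strata and several covariates. When all events fall in one arm, the arm odds ratio has no finite estimate. With few events, the usual large-sample tests do not hold their level.

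The trial is open-label, and the Discussion concedes that this might favour stopping prophylaxis early in the fosfomycin arm. The type of infection is therefore a useful check on the fever endpoint. An infinite odds ratio, or a nominally significant result from a miscalibrated test, would spoil that check for exactly the categories in which it occurs.

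**Working it through.** **The cap on patients.** With success rates of 17% and 30%, a 5-point margin, 80% power and one-sided alpha 0.05, n per arm = (1.645 + 0.842)² × (0.17×0.83 + 0.30×0.70) / (0.13 + 0.05)² = 6.183 × 0.3511 / 0.0324 = 67.0. This reproduces 67 per arm, 134 in all. Then 67 × 1.15 = 77.05, rounded up to 78 per arm, gives the stated 156.

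**Number of coefficients.** Arm + disease + 10 site indicators = 12; with four assumed covariates, 16. Without site: 1 + 1 + 4 = 6.

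**Events available.** Expected febrile patients: 78 × 0.83 + 78 × 0.70 ≈ 119. Assuming one category per febrile patient and an even split over six, each category has about 20 events (13% of 156), which is 20/16 ≈ 1.2 to 20/12 ≈ 1.7 events per coefficient with site. The split is unlikely to be even. If one category took half (an assumption), the other five would average about 12 events (8%). At 3% and 5%, the counts are 156 × 0.03 ≈ 5 and 156 × 0.05 ≈ 8.

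**A check that needs no model.** The chance that at least one arm of 78 has no events at rate p is 1 − [1 − (1 − p)^78]². This gives 37% at p = 2%, 18% at 3%, 3.6% at 5% and 0.05% at 10%.

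**Simulation A.** N = 156, 600 trials per setting, 11 unequal sites with no true site effect, disease and four assumed covariates, ordinary maximum likelihood. An arm estimate counts as infinite if its log odds ratio exceeds 8 in absolute value. Wald figures exclude those runs. Monte Carlo error is about 1 point. All columns are for no true arm effect, except the median odds ratio, for which the true value is 2.

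| Model | Rate | Mean events | Arm OR infinite | LR rejects | Wald rejects | Any coefficient infinite | Median OR (true 2) |
|---|---|---|---|---|---|---|---|
| With site (16 terms) | 3% | 5.1 | 13.3% | 13.0% | 1.0% | 100% | 2.42 |
| | 5% | 8.4 | 4.0% | 10.7% | 4.2% | 100% | 2.22 |
| | 10% | 16.9 | 0% | 6.8% | 5.5% | 98% | 2.25 |
| | 20% | 33.3 | 0% | 5.5% | 5.0% | 75% | 2.14 |
| | 30% | 49.1 | 0% | 4.8% | 3.8% | 49% | 2.23 |
| No site (6 terms) | 3% | 4.9 | 13.8% | 12.0% | 1.4% | 47% | 1.97 |
| | 5% | 8.4 | 3.7% | 9.0% | 2.8% | 16% | 2.12 |
| | 10% | 16.9 | 0% | 5.5% | 4.2% | 0.5% | 2.10 |
| | 20% | 33.1 | 0% | 6.3% | 6.0% | 0% | 2.07 |
| | 30% | 49.3 | 0% | 4.2% | 4.2% | 0% | 2.05 |

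With arm and disease only, the arm estimate is infinite in 17.8%, 3.3% and 0.2% of runs at 3%, 5% and 10%, and the likelihood-ratio test rejects 11.3%, 6.7% and 6.8%. Trimming covariates alone therefore does not cure the rare categories.

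**Simulation B.** Three covariates, true site effects with SD 0.4 on the logit scale, 1,500 trials per setting. With site in the model, at 3%, 5% and 10% the likelihood-ratio test rejects 9.6%, 8.1% and 7.9%, and the Wald test 1.9%, 3.4% and 6.2%. The arm odds ratio is infinite in 11% of null trials at 3% and 1 to 3% at 5%. The median estimate for a true odds ratio of 2 is 2.2 to 2.5. A Firth model with arm and disease rejects 1.5 to 5.3%, with a median estimate of 1.84 to 1.96.

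**A further run** with three covariates gives infinite arm estimates in about 20% and 5% of null trials at 3% and 5%, likelihood-ratio rejection of 14% and 11%, and Firth rejection of 3 to 4%.

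**Overstatement with site terms.** In A, 2.14/2 = 1.07 to 2.42/2 = 1.21. In B, 2.2/2 = 1.10 to 2.5/2 = 1.25. Without site in A, 1.97/2 = 0.99 to 2.12/2 = 1.06.

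**The case against.** The strongest reply is that the article does not fix the model attacked here. It names no covariates, does not say how site is coded, and chooses neither an estimator nor a test. A Firth model is still a logistic model, and such details usually belong in a statistical analysis plan. This is right as far as it goes: leaving those details out is not the fault. What the article does fix is that every category receives a model adjusted for both the strata and other baseline characteristics, with no allowance for rarity.

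Four stronger conclusions that a reader might draw are not supported:

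- **That every infection type is affected.** No rates are given. An even split over six categories gives about 13% each. Outcomes {12} can also be read as four categories, giving 119/4 ≈ 30 events, or 19%. At such rates the arm estimate is almost always finite and the tests are close to nominal, although with site terms the likelihood-ratio test at 10% still rejects 6.8 to 7.9%.
- **That the number of coefficients causes the infinite arm estimates.** They occur about as often without site (13.8% against 13.3% at 3%), and the zero-event calculation involves no model. Sparse events are the main cause. Site terms account for most of the odds-ratio overstatement and nearly all the infinite nuisance coefficients.
- **That false-positive findings would follow.** This applies to the likelihood-ratio test in rare categories. The Wald test errs the other way, and the article names neither.
- **That the overstatement is certain.** It depends on fixed site terms, and the article's two accounts of the stratification disagree.

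It is also fair that the Firth model's rejection rates (1.5 to 5.3%) are little different from the Wald test's in Simulation B (1.9 to 6.2%). Its gain is finite estimates and usable intervals without the likelihood-ratio excess.

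**Conclusion.** The point holds, conditionally. In categories of about 5% or less, the prescribed model fitted by ordinary maximum likelihood gives an effectively infinite arm odds ratio in roughly 2 to 20% of null trials, likelihood-ratio error of about 7 to 14%, and a conservative Wald test. This is so under either account of the strata.

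If the 11 sites are fixed terms, a true odds ratio of 2 is overstated by roughly 10 to 20% (7 to 25% across the settings run), including in categories of 10 to 20%. Some coefficient, mostly a site term, is then infinite in 98 to 100% of trials at rates up to 10%.

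These figures rest on assumed category rates, three or four assumed covariates and ordinary maximum likelihood. This is a secondary analysis with no stated decision rule. The primary comparison, a chi-square test and a difference in proportions, does not depend on it. The change is worth making, but it does not threaten the trial's main conclusion.

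**What to change.** 1. For every infection category, report counts by arm and the risk difference with a 95% CI, stratified by disease (acute leukemia or HSCT).
2. Where events are sparse, replace the fully adjusted model with a Firth-penalised logistic model containing arm and disease, with profile-likelihood intervals.
3. Keep the fuller model only for categories that meet a minimum number of events per coefficient, stated before the infection data are compared by arm. A conventional choice is about 10 patients in the rarer outcome class per coefficient. That requires 20 for arm plus disease and 60 for the six-term model. The 16-term model would need 160, more than the trial enrols, so fixed site terms would be ruled out.
4. Reconcile Trial design {8} with Sequence generation {16a}, so that adjusting for stratification has one meaning.

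The cost is wording only. The statistical price is that site and other covariates go unadjusted in the rare-category models, and that the Firth estimate is pulled slightly towards no effect (median 1.84 to 1.96 for a true 2) and can be conservative at low rates.
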